#### Power and sample size

The primary outcomes of this study are changes in the TUG, 30 Second Chair Stand, and Four Stage Balance tests. These outcomes were selected because they are related to falls risk. Although the aim is to eventually demonstrate a reduction in falls incidence, the Zuni elder population is not big enough to provide adequate statistical power for this outcome. We do plan to extend the follow-up falls calendars to capture these outcomes, and this will provide critical information for future studies. The accepted degree of reduction in falls that is imparted by a traditional OEP is 32% [38, 39]. Because the percent reduction in falls does not directly correlate with a quantitative effect size that will be estimable from the data addressing our primary hypotheses, and because the outcome measures do not perfectly predict the probability of falls, it is likely that the detectable effect size that would be meaningful in the context of reducing falls would need to be a large one in order to suggest that the intervention is likely to have the desired effect on falls incidence. Therefore, the study was powered to detect at least moderate effect sizes. Specifically, we computed the number of participants to enrol into the study that would provide us with at least 80% power to detect an effect size of 0.67 for an improvement in the outcome measures over time between the treatment arms using a two-sided, 0.05 level test of between-group differences over time. Power estimates were obtained from linear mixed effects models that assumed within-subject correlations of 0.3, and within-cluster correlations of 0.1, and also corrected for 3 primary tests of significance. This computation suggested that data from 84 participants in each treatment arm would be required. In order to allow for the potential for dropouts, or for the possibility that the treatment might not be quite as efficacious as desired, 100 study participants per treatment arm will be enrolled. Even if 20% of the participants drop out of the study, this sample size will provide at least 80% power to detect effect sizes of 0.59 – nearly the target of 0.67, and still not a large effect size.

The analysis plan of Aim 4 will utilize linear mixed effects models to compare changes in outcome measurements between treatment arms, as outlined in the analysis plans for Specific Aim 2. These analyses will account for repeated measurements made over time for participants, when appropriate, and will be performed on a data scale that meets modelling assumptions. As in the first aim, an intent-to-treat paradigm will be followed, and sensitivity analyses to examine the impact of drop-out and missing data on the results of the comparisons between groups.

For the power and sample size of Aim 4 we selected the sample size in order to have adequate power for our primary outcomes in Specific Aim 2. With 100 participants per treatment arm, the trial will have 80% power at a two-sided 0.05 level of significance to detect effect sizes of 0.5 in magnitude for changes in quantitative measurement between treatments, even accounting for multiple testing and for potential attrition of up to 20% of the 200 seniors aged ≥ 65 to be enrolled in the trial.

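### The power statement for the primary outcomes contradicts itself: 84 per arm are required for an effect of 0.67, yet 80 per arm are said to suffice for 0.59

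*Protocol article*

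**What the plan says.** All the figures stand in the protocol article under Power and sample size.

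- Target for the three primary outcomes (TUG, 30 Second Chair Stand, Four Stage Balance): "at least 80% power to detect an effect size of 0.67", "using a two-sided, 0.05 level test of between-group differences over time".
- Basis: linear mixed effects models that "assumed within-subject correlations of 0.3, and within-cluster correlations of 0.1" and "also corrected for 3 primary tests of significance". Neither the household cluster size nor the variance of the tested contrast is given.
- Result: "data from 84 participants in each treatment arm would be required".
- Enrolment: "100 study participants per treatment arm will be enrolled", to allow for dropout or for a somewhat weaker treatment effect.
- After a 20% loss: "this sample size will provide at least 80% power to detect effect sizes of 0.59". The text presents 0.59 as falling just short of the 0.67 target.
- Aim 4, same enrolment, allowing for multiple testing and up to 20% attrition: "80% power at a two-sided 0.05 level of significance to detect effect sizes of 0.5 in magnitude". The number of tests, the clustering and the variance are not given.

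**The concern.** A 20% loss from 100 leaves 80 per arm, four fewer than the stated requirement. With the same test, alpha, power, variance and clustering, a smaller sample detects only a larger effect. The plan moves the other way, from 0.67 at 84 to 0.59 at 80. Its comment on 0.59 also treats a smaller detectable effect as a slight shortfall, although being able to detect a smaller effect would be an improvement.

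This paragraph is the justification for the sample size, and readers will use it to judge what a null result on the primary outcomes can exclude. At least one of its figures is wrong on the assumptions it states.

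**Working it through.** **Inputs from the plan:** 0.67 and 84 per arm; 100 enrolled; 20% dropout, so 100 × 0.8 = 80; power 80%; two-sided 0.05 corrected for three tests; within-subject correlation 0.3; within-cluster correlation 0.1. **Assumed:** the correction is Bonferroni (0.05/3), because the method is not named. This gives z = 2.394 + 0.842 = 3.236; uncorrected, z = 2.802.

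**1. Reproducing the 84.** n = 2 × V × DE × (z/d)², with DE = 1 + (m − 1) × 0.1 for cluster size m.
- Plain two-sample test (V = 1, DE = 1): 2 × (3.236/0.67)² = 46.6, so 47 per arm.
- Change score at r = 0.3 (V = 1.4) with an assumed m = 4 (DE = 1.3): 2 × 1.4 × 1.3 × (3.236/0.67)² = 84.9.

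The 84 is therefore approached, but only with a cluster size that the plan does not state.

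**2. Scaling from 84 and 0.67.** With everything else fixed, the detectable effect is proportional to 1/√n, so the unknown variance and cluster size cancel.
- 80 per arm: 0.67 × √(84/80) = 0.687.
- 100 per arm, no dropout: 0.67 × √(84/100) = 0.614.
- n per arm for 0.59: 84 × (0.67/0.59)² = 108.3.

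Power at 80 per arm for effect d is Φ(3.236 × (d/0.67) × √(80/84) − 2.394):

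| d | Alpha 0.05/3 | Alpha 0.05 throughout |
|---|---|---|
| 0.67 | 77.7% | 78.1% |
| 0.59 | 65.0% | 67.3% |

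With 100 per arm and no dropout, power for 0.59 is 76.3% at 0.05/3.

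**3. Can 0.59 be recovered from 84 and 0.67?**
- Favourable rounding (0.665 and 83): 0.677 at 80 and 0.606 at 100. No.
- Dropout that also shrinks households, m to 0.8m: 0.687 × √[(1 + (0.8m − 1) × 0.1)/(1 + (m − 1) × 0.1)] = 0.674 for m = 2, 0.665 for m = 4, 0.649 for m = 10 and 0.626 for m = 50. No.
- Partial data from dropouts: effective n lies between 80 and 100, so the detectable effect is no better than 0.614. No.
- Three-test correction dropped for the second figure only: 0.67 × (2.802/3.236) × √(84/80) = 0.594. Yes, but the plan states no such change.

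**4. Starting from the other figure.** If 0.59 at 80 is right, 0.67 needs 80 × (0.59/0.67)² = 62.0 per arm, not 84.

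**5. Aim 4.** On the Aim 3 assumptions, 0.5 needs 84 × (0.67/0.5)² = 150.8 per arm, and power at 80 is 48.5%. Those assumptions may not apply to Aim 4. A plain two-sample test without clustering at 80 per arm detects z × √(2/80): 0.487 for two Bonferroni-corrected tests, 0.512 for three, 0.528 for four and 0.540 for five. The Aim 4 measures comprise five scores: two SF-12v2 composites, two PROMIS scores and AFRIS.

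**The case against.** The strongest reply is that a contradiction does not identify the wrong figure. A reader might infer that the trial lacks the power it claims. That follows only if 84 for 0.67 is the correct pair, and the 84 is itself reproduced only with an unstated cluster size. If 0.59 at 80 is correct, the stated power stands and the 84 is too high. This objection holds.

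Secondly, simple scaling is not exact here. Loss of individuals shrinks households and lowers the design effect, and under Data analysis plans the mixed models use every measured value, including early visits of those who leave. At a cluster size of about 4, the detectable effect at 80 per arm returns to about 0.67. This also holds, so 78% power at 0.67 and a detectable effect of 0.69 are not safe as replacement text. It does not rescue 0.59, since even 100 per arm with complete data gives 0.61.

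Thirdly, a reader might infer that the Aim 4 figure of 0.5 is impossible. The document does not support that. Aim 4 concerns other outcomes, its variance, clustering and number of tests are not stated, and a plain test gives values close to 0.5. What remains is that 0.5 is not reached on the Aim 3 assumptions, nor by a plain test corrected for three to five outcomes.

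Finally, the plan names a weaker treatment effect as a second reason for enrolling 100. That explains why a smaller effect is quoted, but not how fewer participants could detect it.

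**Conclusion.** The point stands as an internal inconsistency in the primary-outcome power statement: 0.67 at 84 per arm and 0.59 at 80 per arm cannot both hold on the single set of assumptions given.

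If 84 for 0.67 is kept, the detectable effect after 20% dropout is about 0.69 by simple scaling, about 0.67 if household clusters shrink to match, and no better than about 0.61 under any reading of the partial data. Power for 0.59 at 80 per arm is then about 65% by simple scaling, assuming Bonferroni at 0.05/3. If 0.59 at 80 is kept, the requirement for 0.67 is about 62 per arm. An unstated loss of the three-test correction would explain the 0.59, but this is a conjecture. The Aim 4 figure is unsupported as stated rather than shown to be wrong.

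**What to change.** Recompute the sample size for 0.67 and the post-dropout detectable effect in one calculation, with the same alpha (including the three-test correction), cluster size and contrast variance, and state those inputs. Replace 0.59 with the result, which will be no better than about 0.61 if 84 for 0.67 stands. If the recalculation supports 0.59 at 80 per arm instead, correct the 84. Delete the remark that 0.59 is close to the target.

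For Aim 4, recompute the detectable effect with its own number of tests, clustering and variance, state them, and replace 0.5 with the result.

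The cost is one recalculation and the rewording of two paragraphs. The printed figures may become less favourable. No change in enrolment is needed.

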## Discussion

### Spirit of partnership and community engagement

The randomized controlled trial study design comes from numerous conversations and significant compromise on the part of the tribe. In the past, a randomized controlled trial (RCT) design has not been agreed to by the Zuni Pueblo. However, feedback from unsuccessful grant applications clearly demonstrated that this study would not be funded without a RCT study design. We are grateful to the Zuni tribal council for co-designing the current design.

In accordance with the tribal council’s contribution to the study design, all study participants will receive a home safety inspection and offered modification for trip hazards, such as improved lighting (e.g. night lights) and bathtub mats according to guidelines in the STEADI resource Check Your Home for Safety at the beginning of enrolment into the intervention or control group. This is an ethical approach due to the high falls risk in those elder who are randomized to control group and this will be included in our bias assessment.

In the spirit of community engagement and the requirement of the request for proposals, the Zuni community will receive approximately 70% of grant funds over the five years of the study. Up to four Zuni CHR’s and one Zuni coordinator will receive salary support from the grant. Thus, all Zuni research positions will be held by residents of the Zuni Pueblo and all participants will be recruited from within Zuni Pueblo. This assures the Zuni community receives maximum benefits from the trial and continues to grow workforce capacity and skills within the Zuni Pueblo.

According to our existing agreement, all presentations and publications will be reviewed and approved by the Tribal leadership at least 30 days prior to presentation and presented to the Zuni tribe first. Once the trial is completed, we will address local and national dissemination of our results by leveraging resources from UNM’s nationally recognized Project ECHO (Extension for Community Health Outcomes) to make local teleconference presentations to professional and lay audiences. In addition, we will present our scientific results at national and international meetings (Geriatric Society of America, Center for Disease Control and Prevention, Indian Health Service, International Association of Gerontology and Geriatrics, and the New Zealand Association of Gerontology). The Albuquerque Area Southwest Tribal Epidemiology Center will lead the dissemination effort to disseminate findings to rural and urban fall prevention stakeholders along with support by the New Mexico Adult Falls Prevention Coalition and Albuquerque Area Tribal Injury Prevention Coalition. The Falls Coalition is a member of the National Council on Aging Falls Free Initiative, which distributes state fall prevention updates to a national fall’s stakeholder list serve comprised of all state falls coalitions in the US.

Sustainability will be two-fold. We will leverage healthcare insurance payment policies by facilitating Medicaid reimbursement for CHRs and strengthening Indian Health Service (IHS) partnerships to include CHR-delivered OEP into IHS service and referral system. Secondly, the Governor is willing to provide additional support as needed to sustain a successful home based CHR delivered OEP.

### Strengths and limitations

This trial has limitations and strengths. Limitations include that we will not employ a blind assessment, as this would require 4 additional in-person visits and would increase participant burden. Blind assessment is not feasible in this close-knit community. Rather, we will be vigilant in monitoring for assessment fidelity and control for bias by household family unit cluster randomization in the statistical analyses. Another potential limitation is that the OEP is designed for individuals to complete without any additional assistance. If a family member assists an individual in remembering to do the exercises, or how to do the exercises, this will not impact on outcomes. The CHRs will collect information about type and frequency of this type of assistance and this data will be used as a covariant in the analysis.

Strengths include that we brought together a team of qualified investigators who present a unique opportunity to increase understanding of effective approaches to fall risk reduction in an indigenous group with a high burden of fall-related injury. All the investigators have a history of working with indigenous communities both in the US and New Zealand. Another strength is proposing to expand the scope of practice for CHRs by adding fall risk screening and exercise instruction to their available services. The STEADI toolkit offers comprehensive, but simple methods to perform screenings and within the fall prevention research community, appropriate adult falls training content has been developed for CHRs, trialled and free to interested stakeholders. Nevertheless, it remains probable that real and meaningful lifestyle change is unlikely to occur in a sustainable way if individuals do not find internal motivation to modify fall risk factors and continue exercising after the 12-month protocol. The CHRs at Zuni have been shown to effectively implement other health promotion protocols including diabetes and kidney health management. We also conducted a focus group with the current long-term CHRs that demonstrated their enthusiasm for the protocol, a foundation of basic knowledge in exercise and participant safety, and essential cultural knowledge for successful implementation. The rationale behind such internal motivation is likely to vary from person to person, and only through the provision of a flexible, culturally sensitive, person-centered, and carefully considered fall risk management plan will the medical and public health community finally succeed in getting large proportions of elders with elevated fall risk to change their behaviour. Thus, this may prove to be this research protocol’s greatest strength.

#### Confidentiality

Participation in research will involve a loss of privacy, but information about subjects will be handled as confidentially as possible. Representatives of the University of New Mexico Health Sciences Center Human Research Review Committee that oversees human subject research, the Food and Drug Administration or other regulatory agencies will be permitted access to subjects’ records. Also, subject’s participation in the study and information in their study records may be disclosed to their doctors and nurses, and may be disclosed as otherwise provided by law. However, subjects name will not be used in any published reports about this study. Hard copy of all study results will be kept in locked cabinets. Electronic copies of study results will be kept in pass word protected files in computers located in offices of study personnel. Only authorized study personnel, representatives of the NIH and the Human Research Review Committees of the UNMHSC and I H S will have access to study results. The study operates under an NIH Certificate of Confidentiality, which helps researchers protect the privacy of participants in research studies. This certificate means that researchers cannot be forced to tell people who are not connected to this study, including courts, about your participation unless you give written consent. Conducting the study under this Certificate helps to ensure your privacy. In addition, if publications or presentations results from this research, your name or any other personal identifier will not be used.

## Data Availability

The unique research resources established and created in our efforts to develop newly validated methods for fall risk assessment and management / interventions, along with any new Native American specific educational material in Zuni that evolve from the studies, will be available to the scientific community. However, we will follow institutional, tribal, IHS and local IRB guidelines, as well as proprietary mandates. Biological samples are not collected and/or archived for any future studies. We are also committed to sharing other methodological resources with NIH-sponsored projects and coordinating with NIH-supported data coordinating canters as requested. We plan to data readily available to the research community once the experimental and analytical tasks on the studies are complete. We will coordinate data sharing with the NIH and Zuni tribal leadership and make available both the raw data and analysed data upon request from the PIs ([name] and [name]).

## Abbreviations

AFRIS: Attitudes to Falls- Related Interventions Scale
AI: American Indian
CHR: Community Health Representative
CDC: Center for Disease Control and Prevention
CITI: Collaborative Institutional Training Initiative
ECHO: Extension for Community Health Outcomes
IHS: Indian Health Service
OEP: Otago Exercise Programme
PROMIS: Patient-Reported Outcomes Measurement Information System
REDCap: Research Electronic Data Capture
RCT: Randomized Controlled Trial
SF-12v2: Medical Outcomes Study Short Form 12
STEADI: Stopping Elderly Accident Deaths and Injuries
TUG: Timed up and Go
TAP: Tribal advisory panel
UNM: University of New Mexico
UNMCTSC: University of New Mexico Clinical and Translational Science Centre
